### Study objective

In the dose exploration phase I, the safety and tolerability profile of belantamab mafodotin in combination with venetoclax with or without dexamethasone will be evaluated in four different dose levels of the combination treatment. In case of sufficient tolerability and preliminary efficacy, phase I will then be followed by a phase IIa expansion to further evaluate the clinical activity of the combination treatment with the recommended phase 2 dose (RP2D).

The primary objective of the phase I trial part is the establishment of the maximum tolerated dose (MTD) and RP2D of treatment with venetoclax in combination with belantamab mafodotin with or without dexamethasone in patients with RRMM and t(11;14). Further, the safety profile of the combination treatment is comprehensively evaluated. In the subsequent phase IIa trial, the primary objective is assessing the safety and efficacy of the established recommended dose in an expansion cohort. The trial’s secondary objectives include assessing the overall response rate (ORR), MRD negativity rate, PFS, and duration of response (DOR) of the established recommended dose.

### Treatment and selection of doses in the study

The selected dosage regimen was chosen to sequentially assess the safety and efficacy of each dose level combination. The dose escalation phase I follows the traditional 3 + 3 scheme to establish the recommended treatment dose with venetoclax in combination with belantamab mafodotin with or without dexamethasone. The first combination cohort begins with the starting dose, and the remaining cohorts follow with the second to fourth dose, so ideally, 12 patients will be analyzed (Fig. 2). Dexamethasone is added in cohorts 3 and 4 to establish an optimized triplet combination.

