### Sample size

In Phase I of the dose escalation, we employ the standard 3 + 3 design to limit the number of patients exposed to the belantamab mafodotin and venetoclax combination and ensure safety. This approach involves forming cohorts of three patients each. The initial cohort receives the starting dose, followed by subsequent cohorts receiving the second through fourth doses, aiming to evaluate 12 patients (Fig. 2). Dexamethasone is included for cohorts three and four to optimize the triplet combination.

If none of the three patients in a cohort experiences dose-limiting toxicities (DLT), another three patients will be treated at the next higher dose level. However, if one of the first three patients experiences DLT, three more patients will be treated at the same dose level. For the dose escalation phase I, 12–24 patients will be allocated to the trial. The RP2D will be identified based on the safety and preliminary efficacy in phase I.

Phase I will be followed by a cohort expansion phase IIa, which will evaluate the clinical activity of the combination treatment with RP2D in 25 more patients.

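### As described, the recommended phase 2 dose can be accepted on 0 DLTs in 3 patients; the first three expansion patients could complete a six-patient cohort at no extra enrolment

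*Protocol article*

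**What the plan says.** Phase I is a 3+3 design. The Sample size section says "This approach involves forming cohorts of three patients each", and Study objective says that safety and tolerability "will be evaluated in four different dose levels of the combination treatment". The dose section gives the intended size: "so ideally, 12 patients will be analyzed". The Sample size section repeats the aim of 12 and gives a range of 12 to 24.

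Two rules are stated. After 0/3, "another three patients will be treated at the next higher dose level". Otherwise, "if one of the first three patients experiences DLT, three more patients will be treated at the same dose level". Nothing is said about 0/3 at the last level, and no minimum number of patients at the RP2D is given. The RP2D is chosen from phase I safety and early efficacy, on the DSMB's recommendation.

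The next stage is the expansion, "which will evaluate the clinical activity of the combination treatment with RP2D in 25 more patients". For phase IIa, Study objective states that "the primary objective is assessing the safety and efficacy of the established recommended dose in an expansion cohort". Trial conduct and dissemination adds regular DSMB safety reviews.

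**The concern.** Many 3+3 plans ask for six patients at the dose that is carried forward, because three patients say little about a DLT rate. Here the stated 12-patient path closes escalation with three patients at the fourth level. That level has the higher venetoclax dose and dexamethasone together, and the Background says that an anti-BCMA agent with a BCL-2 inhibitor had yet to be investigated. If its true DLT rate is well above what a 3+3 design is meant to accept, 0/3 is still a fairly likely result, and the next planned step is 25 more patients at that dose. The remedy needs no further patients, because those who could supply the missing information are already in the plan.

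**Working it through.** **Reproducing the plan's sizes.** The inputs are four levels, three patients per cohort, six at a level at most, and 25 in the expansion (Study objective; Sample size).

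- Minimum phase I: 4 × 3 = 12. Maximum: 4 × 6 = 24. Largest total: 24 + 25 = 49. All three match the article.
- If six patients were required at the top level, the minimum would be 3 + 3 + 3 + 6 = 15. The stated 12 therefore allows the top level to be accepted on 0/3.

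**What 0/n says about the DLT rate.** The exact (Clopper-Pearson) upper limit for 0/n is 1 − 0.05^(1/n) one-sided, and 1 − 0.025^(1/n) for the two-sided 95% interval.

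- 0/3: 1 − 0.05^(1/3) = 63.2%; two-sided 70.8%.
- 0/6: 1 − 0.05^(1/6) = 39.3%; two-sided 45.9%.

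**How often a level shows 0/3, and what three more patients add.** The article states no target DLT rate, so the true rate p is an assumption, shown from 20% to 50%. Column A is (1 − p)³. Column B is the chance of two or more DLTs in the next three patients, 3p²(1 − p) + p³. After 0/3 this is the same as two or more in six. Column C is A × (1 − B), the chance of 0/3 followed by at most 1/6.

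| True DLT rate p | A: 0/3 | B: ≥2 of next 3 | C: 0/3, then ≤1/6 |
|---|---|---|---|
| 20% | 51.2% | 10.4% | 45.9% |
| 30% | 34.3% | 21.6% | 26.9% |
| 40% | 21.6% | 35.2% | 14.0% |
| 50% | 12.5% | 50.0% | 6.2% |

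For example, at 40%: A = 0.6³ = 0.216; B = 3 × 0.16 × 0.6 + 0.064 = 0.352; C = 0.216 × 0.648 = 0.140.

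**Can the earlier cohorts fill the gap?** Pooling all four levels as 0/12 gives a two-sided upper limit of 26.5%, but only if every level has the same DLT rate. The fourth level exceeds the second by adding dexamethasone, and the third by the higher venetoclax dose. The lower levels therefore do not bound it.

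**The case against.** The strongest reply is that 0/3 does not open 25 places automatically. Expansion is conditional on acceptable tolerability and early efficacy, an interim analysis of phase I is planned, and an independent DSMB that includes a biostatistician recommends the RP2D and then keeps reviewing safety. All of that stands. None of it is a stated step that enlarges a three-patient RP2D cohort, but it does mean that the expansion is overseen.

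Several stronger readings are tempting, and the documents do not support them.

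- A reader might infer that phase IIa has no toxicity threshold. This is a condensed article; Fig. 2, the full protocol and the SAP are not shown, and such thresholds often sit there. Silence in the article does not establish absence.
- A reader might infer that all 25 would be treated however many DLTs occurred. The regular DSMB reviews contradict that.
- A reader might take the Sample size wording to mean that phase IIa looks only at clinical activity. Study objective makes safety part of its primary objective, and the DLT endpoint is not limited to phase I.
- A reader might cite the excess mortality in the placebo-controlled phase 3 venetoclax trial in the Discussion (OS HR 2.03). The same paragraph gives an OS HR of 0.34 in t(11;14) patients, the population enrolled here, with a 95% CI of 0.03 to 3.84. That interval is too wide to settle the matter either way.

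It is also fair to say that 0/3 is only one path, since the RP2D may rest on 1/6. An RP2D below the top level may draw some support from a higher level. The analyses are declared descriptive, and 20 t(11;14) patients have already received venetoclax 800 mg with the same dexamethasone doses, although without belantamab mafodotin.

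**Conclusion.** The point holds as a design improvement. The article's own numbers allow the RP2D to be accepted on 0/3, a result compatible with a DLT rate of up to 63% (one-sided 95%) and seen 34% or 22% of the time when the true rate is 30% or 40%. This follows from the stated minimum of 12 and from the single stated route to six patients, so it does not depend on what the article leaves out.

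The gain from three more patients is real but moderate. At a true rate of 40%, the chance of accepting a level by the 0/3 path without further DSMB discussion falls from 22% to 14%. At 50% it falls from 12.5% to 6%. The conclusion assumes that patients' DLTs are independent and that the full protocol does not already require six patients at the RP2D. If it does, the article's 12 is the figure to correct.

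**What to change.** In Sample size, state that if the RP2D rests on three patients, the first three of the 25 phase IIa patients are assessed for DLTs and complete a six-patient RP2D cohort. State also that the DSMB reviews this cohort before the remaining 22 are enrolled, and that two or more DLTs in six call for a DSMB decision. If the RP2D already rests on six patients, nothing changes. If the full protocol already contains such a step, cite it.

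No patients are added: the total stays between 12 + 25 = 37 and 49. The cost is one enrolment pause of one DLT window, whose length the article does not give, and about a 10% chance of an unneeded DSMB decision if the true DLT rate is 20%.

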**Fig. 2 Fig2:**
[figure not shown]
Trial timeline flow. **A** The dose escalation phase I follows the traditional 3 + 3 scheme. **B** The phase IIa combination treatment scheme includes Belantamab mafodotin, venetoclax, and possibly dexamethasone

The dosing regimen with belantamab mafodotin at 1.9 mg/kg IV every 6 weeks and venetoclax as an oral drug results in a low treatment burden and convenient regimen for patients (Fig. 1).

The reduced 1.9 mg/kg every 6 weeks schedule for belantamab mafodotin was based on emerging data showing a long half-life and durable responses of the substance and was selected to reduce the risk and severity of corneal toxicity while preserving anti-myeloma activity. This schedule represents a substantial de-escalation versus the Q3W schedule of DREAMM-7 and the Q4W schedule of DREAMM-8 [21, 22], which is supported by post-hoc analyses showing that extended dosing may reduce ocular adverse reactions [33]. Subsequent trials, including the phase 3 DREAMM-10 study (NCT06679101) of belantamab mafodotin–lenalidomide–dexamethasone in transplant-ineligible newly diagnosed myeloma, have prospectively adopted Q8W dosing for the first 24 weeks followed by Q12W thereafter [34]. The BELI(E)VE schedule was finalized before these data were available; further interval extension may be evaluated in subsequent studies.

Venetoclax will be given in escalating doses of 400 mg and 800 mg (PO, daily [QD]). Prior data has shown good safety profiles of up to 800 mg QD [26]; however, a lower dose of 400 mg will be assessed first in combination with belantamab mafodotin only.

In the next step, dexamethasone (40 mg PO; 20 mg for patients ≥ 75 years, weekly [Q1W]) will be added to the combination therapy, again starting with the lower dose of venetoclax. The fourth and last cohort of the phase I part will hence assess the combination of belantamab mafodotin (1.9 mg/kg IV Q6W), venetoclax (800 mg PO, QD), and dexamethasone (40/20 mg PO, Q1W) (Table 2).

Based on the results of the Phase I part, the data safety monitoring board (DSMB), consisting of an independent group of two leading experts on MM and one biostatistician, will recommend the dosage for the Phase IIa part (RP2D) (Table 2).

**Table 2 Tab2:** Treatment schedule

Drug	Dose	Route	Days
**Starting Dose level, 6-week-cycle (Q6W)**			
Belantamab mafodotin	1.9 mg/kg	IV	D1
Venetoclax	400 mg	PO	daily (QD)
**Second Dose level, 6-week-cycle (Q6W)**			
Belantamab mafodotin	1.9 mg/kg	IV	D1
Venetoclax	800 mg	PO	daily (QD)
**Third Dose level, 6-week-cycle (Q6W)**			
Belantamab mafodotin	1.9 mg/kg	IV	D1
Venetoclax	400 mg	PO	daily (QD)
Dexamethasone	40 mg (20 mg for subjects ≥ 75 years)	PO	weekly (Q1W)
**Fourth Dose level, 6-week-cycle (Q6W)**			
Belantamab mafodotin	1.9 mg/kg	IV	D1
Venetoclax	800 mg	PO	daily (QD)
Dexamethasone	40 mg (20 mg for subjects ≥ 75 years)	PO	weekly (Q1W)

### Trial assessments

A baseline assessment is performed within 30 days before treatment (Table 3), including an ocular exam, skeletal survey, extramedullary plasmacytoma assessment, bone marrow biopsy, and measurable disease evaluation. During treatment, an assessment is performed as described in Table 3 for every cycle, including response to treatment evaluation. Bone marrow analysis will be done every fourth cycle (= every 6 months) and at progression, with a central laboratory assessing MRD status. At the end of the treatment (EOT) for each patient, a final assessment should be made according to Table 3. The follow-up will be continued as part of a non-interventional follow-up (Table 3). All patients will enter a follow-up period during which toxicity, remission state, and anti-myeloma treatment parameters will be documented.

**Table 3 Tab3:** Study assessments

**Study Assessments**				
	Baseline	During treatment	EOT	Follow up ^17^
Informed Consent	X			
Inclusion/Exclusion criteria	X			
Demography	X			
Medical History (includes substance abuse)	X			
Full physical exam, Vital Signs (BP, HR, Body Temperature) and ECOG Performance Status	X	X	X	
Ocular Exam ^1^	X	X	X	X
Weight and Height	X	X	X	
Education about life style considerations for the study	X	X	X	
Past and current medical conditions	X			
Concomitant Medication	X	X	X	
Quality of Life Questionnaire	X	X	X	
Serum Pregnancy Test (WOCBP only) ^2^	X	X	X	X
Hematology ^3^	X	X	X	
Blood clinical chemistry, Thyroid function tests, Estimated Glomerular Filtration (eGFR) ^4,5,6^	X	X	X	
Urine Dipstick	X	X	X	
Spot Urine (albumin/creatinine ratio) or urine dipstick ^7^	X	X	X	
HIV, HBsAG, HBcAG, HCV test ^8^	X			
12-lead ECG ^9^	X	X	X	
Echocardiography (LVEF) ^10^	X	X#	X#	
ß2 Microglobulin	X	X	X	
UPEP 24 h urine collection	X	X	X	
Urine immunofixation	X	X	X	
SPEP ^11^	X	X	X	
serum immunofixation	X	X	X	
serum FLC assay ^12^	X	X	X	
IgG, IgA (IgD or IgE, if applicable ^13^)	X	X	X	
Calcium corrected for albumin (serum)	X	X	X	
Skeletal survey (Whole-body Low dose Osteo CT) ^14^	X	X#		
Extramedullary Plasmocytoma Assessment (by whole body CT or whole-body MRI or CT/PET) ^15^	X	X	X	
BM (biopsy or aspirate) for local disease assessment	X	X	X	
BM aspirate (central lab) for cytogenetics/ FISH testing, MRD testing and CTC assessment^16^	X	X^16^	X	
Peripheral blood (central lab)	X	X	X	
Adverse Events ^18^		X	X	X
Ocular Prophylaxis		X		
Dosing of study medication		X		

X = perform

# = perform if clinically indicated

1. Screening ocular examination will be performed by an ophthalmologist (or optometrist, if an ophthalmologist is not available) within 30 days prior to C1D1 and shortly before dosing for the first 6 cycles (window allowed is up to 5 days prior to each dosing visit. All efforts should be made to schedule as close to Belantamab Mafodotin dosing as possible). After the 6th cycle of Belantamab Mafodotin, if there are no significant ocular symptoms or vision changes, the frequency of ophthalmic exams may be decreased to every 3 months until the end of treatment. In cases of persistent or newly developed ocular symptoms, the participants will have further ophthalmological exams at least every 3 months until resolution to grade 1 or baseline or more frequently as clinically indicated by the eye care specialist

2. Perform only in women of child-bearing potential. Two serum pregnancy tests should be performed at screening. The first test should be performed at least 10 days prior to C1D1 and the second test within 24 h prior to administration of C1D1. Further serum pregnancy tests should be performed within 48 h prior to each dose. Final pregnancy test (serum or, in this case, urine) must be performed in WOCBP at least 70 days after the last dose of IMP, preferably at a visit. Follow up pregnancy assessment by telephone (for WOCBP only) should be performed 4 months after the last dose of Belantamab Mafodotin

3. hematology: hemoglobin, leukocyte count (differential count), platelets

4. blood chemistry: total proteins, albumin, creatinine, GOT/AST, GPT/ALT, γ-GT, urea, total bilirubin, alkaline phosphatase, LDH, CRP, calcium, sodium, potassium, uric acid, serum glucose

5. TSH, free T3 and T4

6. eGFR as calculated by Modified Diet in Renal Disease (MDRD) formula

7. Urine dipstick for protein may be used to assess for presence of urine protein. Albumin/creatinine ratio needs to be done in any participant with urine dipstick result of ≥ 1 + at screening, or with positive protein if urine dipstick protein quantification is not available

8. Hep C RNA testing is optional, but it may be performed to determine participant eligibility if Hep C antibody positive. If negative, patient is eligible

9. ECG on C1d1 + d8 and C2d1 only

10. ECHO may be performed within 30 days prior to C1D1

11. SPEP and UPEP will include M protein calculations

12. Serum Free Light Chain assay will include kappa/lambda ratio and quantification of involved and uninvolved light chains

13. IgD/IgE testing is only required for patients with IgD/IgE myeloma

14. Skeletal survey results within 30 days prior to C1D1 may be used for screening. Same modality used at Screening should be used throughout study. During treatment skeletal Survey at the time of suspected disease progression or as clinically indicated. Same modality used at Screening should be used throughout study

15. In participants with known or suspected extramedullary plasmacytoma, a whole-body scan (i.e., CT, MRI, or PET-CT) should be performed within 30 days prior to C1D1. The same method should be used throughout the study. Selected target lesion needs to be measured and followed over time. Further extramedullary plasmocytoma assessment as clinically indicated, or to confirm PD, imaging with PET/CT or Osteo-CT or WB-MRI may be performed by the same method throughout the study as was done at baseline

16 BM analysis mandatory on Cycle 4d1, C8d1, C12d1 and at PD. BM analysis may be done within 5 days before the mentioned time points. At these defined time points, also peripheral blood samples need to be collected. Additional BM analyses shall be performed as necessary to confirm response status (e.g. CR/sCR) according to IMWG

17. The survival for MM including data for subsequent MM therapies and remission state will be documented in medical charts. No visit necessary. Contacts will be made via phone calls, emails or other means of communications every 12 weeks until disease progression. After disease progression, only survival or date and cause of death will be documented every 6 months until end of the trial. Participant does not need to come in for visit unless they are being followed for corneal signs that are present at the end of study treatment

18. AEs/SAEs will be collected up to 70 days after the last dose of study treatment. All AEs/SAEs will be followed until the event is resolved, stabilized, otherwise explained, or the participant is lost to follow-up

As indicated in Table 3, quality of life questionnaires EQ-5D, QLQ-C30, and QLQ-MY20 are collected from all participants at baseline and additional time points.

### Ocular toxicity prevention and management

Given the known risk of corneal events with belantamab mafodotin, the protocol mandates baseline ophthalmologic examination and pre-dose ophthalmologic assessment for the first 6 cycles, with subsequent assessments every 3 months in the absence of significant findings. All participants receive prophylactic preservative-free artificial tears (4–8 times daily from Cycle 1 Day 1 through the end of belantamab mafodotin treatment) and are offered cooling eye masks during infusion. Contact lenses are prohibited during study treatment. Belantamab mafodotin dose modifications (continuation, dose hold until resolution, or dose reduction) follow the Keratopathy Visual Acuity (KVA) Scale, integrating ophthalmologic examination findings, best-corrected visual acuity, and patient-reported symptoms. Participants with persistent corneal findings at EOT are followed monthly for up to 12 months or until full resolution of findings.

### Infection prevention

Anti-infective prophylaxis is recommended for all participants for at least the first 12 weeks of treatment and for at least 30 days following disease progression, using amoxicillin/clavulanic acid, levofloxacin, or an institution-specified equivalent. Antiviral (HSV/VZV) and *Pneumocystis jirovecii* (PJP) prophylaxis are administered throughout study treatment at investigator discretion per institutional guidelines.

### Study outcomes and endpoints

The primary endpoint is defined as (I) percentage (number) of patients with dose-limiting toxicities (DLTs) with DLTs defined as: (a) prolonged neutropenia grade 4 for more than ten days, (b) prolonged thrombocytopenia grade 4 for more than seven days, (c) any grade 4 non-hematologic toxicity, (d) and any grade 3 reported non-hematological toxicity, which is assigned with a possible relationship to the applied study drugs as reviewed by the Data Safety Monitoring Board (DSMB); and (II) the percentage (number) of participants with adverse events (AEs), changes in clinical signs and laboratory parameters. AEs will be graded according to Common Terminology Criteria of Adverse Events (CTCAE) v5.0.

Secondary efficacy endpoints are overall response rate (ORR), rates of IMWG responses, minimal residual disease (MRD) negativity (sensitivity 10^− 5^) rate, PFS, duration of response (DOR), and health-related quality of life assessments as a patient-reported outcome.

Assessment of circulating tumor cells (CTC), investigations of mitochondrial activity, and single-cell analyses for immunophenotyping will be investigated as exploratory biomarkers.

### Statistical considerations and data handling

The trial is designed as a phase I/IIa study to analyze the safety of venetoclax and belantamab mafodotin as the primary endpoint.

### Sample size

In Phase I of the dose escalation, we employ the standard 3 + 3 design to limit the number of patients exposed to the belantamab mafodotin and venetoclax combination and ensure safety. This approach involves forming cohorts of three patients each. The initial cohort receives the starting dose, followed by subsequent cohorts receiving the second through fourth doses, aiming to evaluate 12 patients (Fig. 2). Dexamethasone is included for cohorts three and four to optimize the triplet combination.

If none of the three patients in a cohort experiences dose-limiting toxicities (DLT), another three patients will be treated at the next higher dose level. However, if one of the first three patients experiences DLT, three more patients will be treated at the same dose level. For the dose escalation phase I, 12–24 patients will be allocated to the trial. The RP2D will be identified based on the safety and preliminary efficacy in phase I.

Phase I will be followed by a cohort expansion phase IIa, which will evaluate the clinical activity of the combination treatment with RP2D in 25 more patients.

